## Introduction

### Overview

Multiple sclerosis (MS) is a common, immune-mediated, demyelinating disease that affects the central nervous system. MS has a highly variable course; therefore, patient-specific treatment decisions are becoming increasingly important. Currently, we have no way to differentiate between the patients who will acquire rapid disability progression and the ones who will remain stable over several years. Most studies point toward early intervention giving a better long-term outcome; however, long-term immunosuppression is associated with increased adverse risk [1,2]. Generally, MS therapies are long-term and some have a demonstrated rebound phenomenon precluding them from being stopped for long periods of time, such as fingolimod [3] and natalizumab [4]. However, there are currently 2 drugs that can potentially be used for immune reconstitution treatment: alemtuzumab and cladribine.

Alemtuzumab is administered in 2 courses, via infusion, 1 year apart. In the Comparison of Alemtuzumab and Rebif Efficacy in Multiple Sclerosis Study (CARE-MS) extension trial, a redosing scheme was introduced, with up to 4 additional doses being offered in the event of recurring clinical activity [5]. Cladribine is a synthetic purine analog, and its mechanism of action is thought to be primarily via induction of apoptosis in lymphocytes [6]. It was shown in a phase III trial (A Safety and Efficacy Study of Oral Cladribine in Subjects with Relapsing-Remitting Multiple Sclerosis; CLARITY) to be highly effective in controlling disease activity [7-10]. With a no evidence of disease activity 3 (NEDA 3) rate of 44% over 2 years [7], it is placed in the range of the most efficacious disease-modifying therapies (DMTs) along with alemtuzumab (39%) [11,12] and ocrelizumab (47%) [13]. Furthermore, after 2 years of treatment and 2 years of follow-up (treatment free), 75% of patients with MS remained relapse free [8,14]. However, clinical stability beyond year 4, and additional doses of cladribine tablets based on clinical activity, has not yet been studied.

In the study discussed below*,* we will offer additional doses of cladribine tablets after 3 years. We aim to compare the clinical outcomes of patients with MS who received additional doses of cladribine with those who changed DMT. We also aim to identify biomarkers for disease control that can be used for treatment decisions, such as redosing with cladribine tablets versus change of DMT.

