#### DNA Methylation

Epigenome-wide DNA methylation will be evaluated using DNA extracted from frozen whole blood samples. Genomic DNA will be bisulfite converted and hybridized to Illumina Infinium MethylationEPIC BeadChip arrays at the lead site. Changes in DNA methylation (differentially methylated positions) will be expressed as population medians. Medians will be used to identify changes between responders and nonresponders that meet both the significance cutoff of *P*<.05, and a threshold of >10% change.

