### Statistical Methods

#### Sample Size Calculation

This is a longitudinal study of 150 patients with MS entering the study and predicted to have no more than 20% dropout. Over the study period, we expected 120 patients with MS with longitudinal data for all measured factors: clinical, cellular, and omics. On the basis of CLARITY and CLARITY extension study data, we expect approximately 50% of patients with MS (n=60) to exhibit disease activity according to NEDA 3 (ie, nonresponders) [7-10].

We performed a detailed simulation analysis to assess the power of our sample sizes to detect significant associations at a range of effect sizes and for a range of significance thresholds as per the recommendations of Tsai and Bell [45]. With 120 cases (60 responders vs 60 nonresponders), this study will have 80% power to detect a minimum mean biomarker difference of 10% at a Benjamini-Hochberg false discovery rate of 0.05, which will reasonably balance type I and type II errors. To detect more minor differences, we will use a penalized regression analysis within a machine learning framework using the GLMNet tool [46]. This method is designed for studies with large numbers of predictors and will further enhance the power to identify multi-marker signatures that are predictive of patient response (see details below in the *Association Modeling* section).

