#### Association Modeling

Our primary outcome is treatment response status according to NEDA 3. We will perform parametric statistical analysis to determine whether any clinical parameters are associated with outcome—the dependent variable. Multiple repeated measurements of the same individual will be obtained. Therefore, we will apply generalized linear mixed models for binary outcomes, with random effects for time points to account for within-subject correlations and clustering. Clinical factors included in the primary analysis will be EDSS, MRI, and relapse rate measures regressed at baseline. Confounding factors (age, sex, disease duration, etc) will be included as required. By carefully defining covariate values in terms of lagged or leading indicators of study factors, longitudinal data will help us to establish the direction of causation and any lags involved. We will also use Mendelian randomization techniques to help dissect causation from the correlation of evidence for causality. In this analysis, all predictor biomarker variables will be modeled individually and yield a test-specific (unadjusted) *P* value. However, we will apply a Benjamini-Hochberg false discovery rate to adjust the raw *P* value for multiple testing while maintaining power. The secondary outcome variables will be modeled similarly using mixed models with specific parameters dependent on the type of data.

To identify multi-biomarker signatures that predict response in this patient cohort, we will also use machine learning algorithms on the patient cohort data set. Specifically, elastic-net regularized generalized linear model analyses using logistic, linear, or multinomial or Poisson models (depending on the outcome variable) will be conducted within a cross-validation routine to avoid overfitting. This will be performed on the entire factor set using the GLMNet package in the R program [46]. Briefly, GLMNet fits a generalized linear model via penalized maximum likelihood and is akin to a stepwise forward regression with the added feature of being able to perform internal cross-validation. GLMNet allows for both binary and multinomial outcomes. GLMNet allows for the rapid discovery of reduced factor panels that are likely to be associated with outcomes. This complementary approach is not susceptible to multiple testing burdens and will facilitate the identification of the best fitting multifactor signature that is predictive of treatment response [46].

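### The multi-marker elastic net has no stated handling of the clinical predictors and no clinical-only benchmark, so its own performance will not show what the biomarkers add

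*Protocol article*

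**What the plan says.** All references are to the protocol article.

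- Introduction, Overview, gives the purpose: "We also aim to identify biomarkers for disease control that can be used for treatment decisions". The example there is redosing with cladribine versus changing therapy.
- Sample Size Calculation describes the data: "we expected 120 patients with MS with longitudinal data for all measured factors: clinical, cellular, and omics".
- DNA Methylation sets the scale of the omics part: "Epigenome-wide DNA methylation will be evaluated using DNA extracted from frozen whole blood samples".
- Association Modeling describes two analyses. The first is a mixed model for NEDA 3 status: "Clinical factors included in the primary analysis will be EDSS, MRI, and relapse rate measures regressed at baseline", and "Confounding factors (age, sex, disease duration, etc) will be included as required". Biomarkers are then modelled one at a time with false discovery rate control.
- The second is the elastic net: "This will be performed on the entire factor set using the GLMNet package in the R program". It is described thus: "GLMNet fits a generalized linear model via penalized maximum likelihood and is akin to a stepwise forward regression". Validation is internal, since the fits "will be conducted within a cross-validation routine to avoid overfitting".

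For the elastic net, the article states no forced-in terms, penalty factors or predictor blocks. It names no reference model and no measure of incremental performance.

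**The concern.** EDSS, relapse history and MRI are available in every MS clinic. A biomarker helps a treatment decision only if it improves on them. The plan puts those factors and the array into one fit and judges the result by its own cross-validated performance. Two things can go wrong.

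- If every predictor carries the same penalty, a handful of informative clinical factors compete with a very large number of array positions in about 120 patients. They can be dropped in favour of chance associations.
- Even if the fit performs tolerably, its performance is that of the mixture. A marker that only mirrors baseline disease activity can lift it above chance and add nothing.

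Without a clinical-only model on the same folds, neither failure can be told apart from a useful signature. The cost falls on the aim of finding biomarkers for redosing decisions. The mixed-model analysis of NEDA 3 is not affected.

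**Working it through.** **The plan's own counts.** 150 × (1 − 0.20) = 120 patients with data, and 120 × 0.50 = 60 nonresponders. Both agree with Sample Size Calculation. The plan gives no performance figure for the elastic net, so there is none to reproduce.

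**Assumed inputs.** The article gives no effect sizes and no number of array positions. The following are assumptions.

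- Four independent clinical predictors: three with odds ratio 1.8 per SD, and one with half that log-odds, exp(0.5 × ln 1.8) = 1.34.
- 500 or 5,000 markers.
- 120 training patients, with an average event rate of 50%.
- Logistic elastic net with mixing value 0.5 and the penalty chosen by 5-fold cross-validation.
- AUC measured in 2,000 new patients, averaged over 40 runs (500 markers) or 25 runs (5,000 markers).

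Three scenarios were run: (1) no marker carries information; (2) 20 markers are proxies, each correlated 0.6 with one clinical factor, and add nothing; (3) five markers truly add, with odds ratio 1.8 each.

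| Scenario | Markers | AUC, clinical only | AUC, one common penalty | AUC, clinical unpenalised + penalised markers | AUC, markers only | Clinical terms kept (of 4) under common penalty |
|---|---|---|---|---|---|---|
| 1 | 500 | 0.740 | 0.573 | 0.735 | 0.499 | 1.73 |
| 1 | 5,000 | 0.731 | 0.527 | 0.728 | 0.501 | 0.64 |
| 2 | 500 | 0.740 | 0.586 | 0.735 | 0.553 | 1.70 |
| 2 | 5,000 | 0.731 | 0.535 | 0.728 | 0.514 | 0.68 |
| 3 | 500 | 0.682 | 0.613 | 0.701 | 0.577 | 1.38 |
| 3 | 5,000 | 0.685 | 0.519 | 0.691 | 0.517 | 0.16 |

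**Loss under a common penalty** (clinical only minus common penalty):

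- Scenario 1: 0.740 − 0.573 = 0.167 and 0.731 − 0.527 = 0.204.
- Scenario 2: 0.740 − 0.586 = 0.154 and 0.731 − 0.535 = 0.196.
- Scenario 3: 0.682 − 0.613 = 0.069 and 0.685 − 0.519 = 0.166.

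The combined fit predicts worse than the clinical factors alone in all six settings, including those where five markers truly add.

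**What the benchmark shows** (clinical unpenalised plus markers, minus clinical only):

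- Scenario 1: 0.735 − 0.740 = −0.005 and 0.728 − 0.731 = −0.003.
- Scenario 2: the same, −0.005 and −0.003.
- Scenario 3: 0.701 − 0.682 = +0.019 and 0.691 − 0.685 = +0.006.

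With 500 markers, the combined fit's own AUC is 0.586 when markers are mere proxies and 0.613 when some truly add. Those two values do not tell a reader which situation applies. The change against clinical-only has the opposite sign in the two cases. It is small, so one trial will estimate it imprecisely.

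**A second simulation with other assumptions** used three clinical factors with joint AUC 0.70, 20 cell or serum markers of which one differs by 0.5 SD, and 1,000 or 20,000 independent noise positions. The combined fit reached 0.57 and 0.53, against 0.69 for clinical-only.

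**The case against.** A reader might infer that the trial cannot say whether any biomarker adds to clinical information. The article does not support that. Its mixed model names baseline EDSS, MRI and relapse rate, allows confounders, and then tests biomarkers individually. The natural reading is one marker at a time beside the clinical factors, although the wording does not make clear that those factors stay in every marker model. What remains is that an adjusted association for one marker is not a gain in prediction and says nothing about the multi-marker signature.

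A reader might also infer that a single penalty and the unscreened array are fixed by the plan. Both are inferences. The article is silent on penalty factors, which the software permits. It also gives methylation its own screen (P<.05 and more than 10% change) without saying whether screened or all positions enter the elastic net. Likewise, that no comparison is made can mean only that none is described here; a fuller plan may contain one. What the article does fix is the predictor set, and a fit to that set as described carries the risk shown above.

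An AUC of 0.53 to 0.57 would be seen as poor without a benchmark. That is fair for those values, but 0.61 against an unreported 0.68 would not be recognised as a loss.

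The elastic net is presented as a complementary discovery step. That limits the severity. It does not remove the need for a benchmark when the stated use is treatment decisions.

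Finally, the simulations assume their effect sizes, use one mixing value, and mostly give the markers little or nothing to contribute. They show the mechanism, not the size to expect in this trial.

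**Conclusion.** The point holds in a limited form. The elastic net is specified on clinical, cellular and omics factors together, in about 120 patients, with no stated handling of the clinical terms and no clinical-only benchmark. If it is run with default penalisation, the baseline clinical factors can be shrunk out among array markers. In any case, its own cross-validated performance will not show added value. Under the assumed effects in the first simulation, the AUC loss against clinical-only ranged from about 0.07 to 0.20, and unpenalised clinical terms removed it. These sizes depend on the assumed odds ratios, marker counts and independence of markers. The case for a benchmark does not depend on them. This is worth correcting before the signature analysis is run; it does not undermine the primary analysis.

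**What to change.** In Association Modeling, state that:

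1. the baseline clinical factors (EDSS, MRI, relapse rate and age) stay in the elastic net unpenalised (penalty factor 0);
2. the biomarkers are penalised, and methylation may have its own penalty;
3. a clinical-only model is fitted on the same folds, with the penalty of the full model tuned inside them;
4. the result reported is the cross-validated change in AUC or log-loss against the clinical-only model, with its uncertainty;
5. a signature is described as useful for treatment decisions only if it improves on the clinical-only model.

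If each clinical factor is one term, four unpenalised terms with 60 nonresponders give 60 / 4 = 15 events per term. The MRI measures should therefore be few and named in advance. It would also help to say whether the clinical factors stay in each single-marker mixed model.

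The cost is analysis wording and a few extra fits on data already planned; no visit or sample changes. The downside is a possibly less favourable headline if the biomarkers add little.

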**Conclusions:**

This will be the first long-term efficacy trial of cladribine, which offers reinitiation of therapy in the 3rd year, based on disease activity, after the initial 2 courses. We expect that this study will indicate whether any of the assessed biomarkers can be used to predict treatment efficacy or the need for future reinitiation of cladribine in people with MS.

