**Inclusion criteria**
Participants must be eligible for and already intend to commence cladribine tablets in accordance with the Australian Product Information (PI). Cladribine tablets are indicated for relapsing remitting patients with multiple sclerosis who do not have HIV infection, active chronic infection, are immunocompromised, have severe renal impairment, or are pregnant or breastfeeding.Participants must have the ability to understand the purpose and risks of the study, as outlined in the patient informed consent form and provide signed and informed consent and authorization to use protected health information in accordance with national and local privacy regulations.The participants must meet the McDonald criteria [43] for the diagnosis of relapsing remitting multiple sclerosis.Male or female participants aged 18-70 years.Be able to provide details for or consent to provide access to a stored minimum data set (ie, demographics, date of diagnosis, relapse information, and baseline expanded disability status scale score).Be able and willing to comply with all study procedures, including magnetic resonance imaging scanning, as per the protocol.Must agree to use contraception from baseline until 6 months after the last dose of cladribine tablets, unless they or their partners are infertile or surgically sterile.Participants must be aware of all precautions listed in the PI for Mavenclad, and any subsequent disease-modifying therapy treatment received within this clinical study must be adhered to.

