### Assessments

#### NEDA Status

NEDA-3 and NEDA-4 status (absence of clinical relapses, confirmed disability worsening, and new T2 lesions, including brain atrophy [NEDA-4 only]) will be assessed based on the clinical data uploaded into the database (MSBase) [44]. For this study, we will use the NEDA-4 criteria as defined by Kappos [16]. Physical examinations, vital sign assessments, and expanded disability status scale (EDSS) assessments will be performed throughout the study. Concomitant medications and adverse events are assessed at every study visit. On the basis of clinical and MRI parameters, patients with MS will be classified as NEDA-positive (responders) or NEDA-negative (nonresponders).

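### Markers associated with NEDA in this all-treated cohort are prognostic for activity on cladribine; the planned models cannot show that a marker predicts treatment benefit or can guide redosing versus a change of DMT.

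*Protocol article*

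**What the plan says.** Only the protocol article is available.

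- **Who is studied.** Inclusion criteria: "Participants must be eligible for and already intend to commence cladribine tablets in accordance with the Australian Product Information (PI". No group starts on another treatment or on none.
- **What response means.** NEDA Status: on clinical and MRI parameters, "patients with MS will be classified as NEDA-positive (responders) or NEDA-negative (nonresponders"). Association Modeling uses NEDA 3 as the treatment-response outcome.
- **What is fitted.** Association Modeling specifies mixed models for the binary outcome. EDSS, MRI and relapse rate at baseline are included, and confounders such as age, sex and disease duration are added as required. Biomarkers are entered one at a time with Benjamini-Hochberg control, and an elastic net is then run on all factors. No marker-by-treatment or marker-by-strategy term is described.
- **What is concluded.** The elastic net is to allow "identification of the best fitting multifactor signature that is predictive of treatment response".
- **What it is for.** The Introduction (Overview) aims to "identify biomarkers for disease control that can be used for treatment decisions, such as redosing with cladribine tablets versus change of DMT". The abstract's Conclusions expect to learn "whether any of the assessed biomarkers can be used to predict treatment efficacy or the need for future reinitiation of cladribine". The Objective section also lists prediction of disease activity and of the need to redose.

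**The concern.** A marker can be associated with NEDA in treated patients for two different reasons. It may mark patients who would have little activity under any management (prognostic), or it may mark patients in whom cladribine works better (effect-modifying). Only the second supports choosing a treatment by the marker. The planned models see the marker and the outcome in treated patients only, so they cannot tell the two apart.

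The Introduction goes beyond loose use of the word response, because it names a choice between two strategies. If the plan is followed as written, a marker that forecasts the same outcome after redosing as after switching could be reported as a guide to that choice.

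**Working it through.** **1. The plan's own figures.** Sample Size Calculation describes a "longitudinal study of 150 patients with MS entering the study and predicted to have no more than 20% dropout", and says "we expected 120 patients with MS with longitudinal data for all measured factors". 150 × (1 − 0.20) = 120, and 50% of 120 gives 60 v 60. These reproduce. The stated 80% power for a 10% mean difference cannot be reproduced, because the article gives neither the marker SD nor the number of tests. At unadjusted two-sided 0.05 it would need a standardised difference of √(2/60) × (1.960 + 0.842) = 0.51. The point below does not depend on this.

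**2. What the models can identify.** Let X be a standardised marker, T = 1 for cladribine and Z the baseline covariates:

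logit P(NEDA) = a + t·T + b·X + c·X·T + d·Z

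Here b is the prognostic part and c the effect-modifying part. With T = 1 for everyone this becomes

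logit P(NEDA) = (a + t) + (b + c)·X + d·Z

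Only b + c can be estimated. The pair b = 0.54, c = 0 and the pair b = 0, c = 0.54 give the same data. Including Z does not separate them, and neither does FDR control or cross-validation. Lagged covariates and Mendelian randomization address whether the marker causes the outcome, not whether it modifies the drug's effect.

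**3. Illustration.** 20,000 simulated cohorts of 120, NEDA rate held at 50%, slope 0.54 log odds per SD (assumed, chosen to give about 80% power), two-group test at unadjusted 0.05:

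| Marker | Test significant |
|---|---|
| Prognostic, no drug effect | 80.9% |
| Prognostic, uniform drug effect | 81.1% |
| Pure effect modifier | 80.6% |
| Unrelated to outcome | 5.1% |

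What matters is that the first three rows agree. Their level reflects the assumed slope and threshold and is not a forecast for this trial. At a threshold of 0.001 the first row falls to 31%.

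**4. What a treatment contrast would offer.** Two strategies, redosing and changing DMT, will occur from the year-3 decision onward. The article does not give their sizes; 30 v 30 is assumed. A logistic marker-by-strategy interaction test at two-sided 0.05 rejects in:

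| Interaction (log odds per SD) | Rejections |
|---|---|
| 0 | 4% |
| 0.55 | 13% |
| 1.1 | 41% |

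It keeps its error rate for a purely prognostic marker, but its power is low. These runs allocate strategy at random, so they leave out confounding.

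**5. Outcome for that contrast.** Study Design makes relapse or new MRI activity the indication for redosing. End Points sets NEDA at 6 years relative to screening. If NEDA is read cumulatively, a patient redosed for activity has already lost it, so the outcome cannot show whether redosing worked. Activity has to be counted from the decision.

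**The case against.** **Response is defined operationally.** On the article's own definitions, predicting response already means predicting NEDA on cladribine. This holds for much of Association Modeling. It does not cover the efficacy wording in the abstract or the choice between redosing and switching in the Introduction.

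**Prognosis is the right tool for some stated aims.** This stands in full. Redosing is prompted by disease activity, so a prognostic marker can properly forecast activity and the need to redose. The abstract's clause on reinitiation and the matching parts of the Objective need no change.

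**The plan already adjusts for severity.** This also stands as far as it goes. In a check with NEDA driven only by a measured severity score (assumed log odds 1.0 per SD, n = 120), a marker correlated 0.5 to 0.7 with severity was significant in about 60% to 90% of runs unadjusted, but only 4% to 5% adjusted. A marker that merely tracks measured mild disease would therefore largely be screened out. Adjustment still supplies no treatment contrast.

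**A stronger reading is tempting.** A reader might infer that the rule declares predictors just as often when cladribine does nothing, in some 81% of trials. The documents do not support that. The figure needs unadjusted 0.05, whereas the plan specifies Benjamini-Hochberg control with an epigenome-wide array among the markers. Its effect size was chosen to give about 80% power, so the level is circular. It also fixes NEDA at 50%: if an ineffective drug lowered NEDA to 40%, 30%, 20% or 15%, the rate would be 79%, 73%, 61% or 53%.

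**An interaction term may be left to the full protocol.** Its absence from an article would be no finding on its own. The point is that the article states a use which the analysis it describes cannot support.

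**Conclusion.** The concern holds in a limited form. The planned models give markers prognostic for NEDA on cladribine. That is valid for forecasting disease activity and the need to redose. It does not support the treatment-efficacy statement in the abstract or the use of markers to choose redosing over a change of DMT.

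This rests on the all-treated design and the definition of response, both stated in the article, and on no assumed figure. The error cannot be sized as a false-positive rate for this trial, since marker SDs, the number of tests and the strategy group sizes are not given. The 13% to 41% power range depends on the assumed 30 v 30 split and effect sizes. It shows only that a proper treatment-selection analysis here would be exploratory. The point is worth correcting before analysis, and the main cohort analysis is unaffected.

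**What to change.** 1. In Association Modeling, in the treatment-efficacy clause of the abstract's Conclusions, and in the Introduction's statement on redosing versus change of DMT, describe the result as prognostic for NEDA on cladribine. Leave the aims of forecasting activity and the need to redose as they are.
2. Reserve any treatment-selection claim for an exploratory marker-by-strategy interaction, redosed v switched, from the year-3-or-later decision onward. Use:
   - the last marker value before the decision;
   - disease activity re-baselined at the decision as the outcome;
   - adjustment for what drives the clinical choice: EDSS, recent relapse and MRI activity, age, disease duration and prior DMT.
3. Report the interaction with a confidence interval and label it exploratory.

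The cost is wording and one additional model on data the study already plans to collect; no visit, sample or treatment changes. The downside is a more modest claim and an imprecise interaction estimate, with residual confounding possible because strategy is chosen clinically.
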